## **6. Study tools**

The intervention will include: (i) standard information about rotavirus infection (same as that for the controls) (ii) key information about rotavirus infection and vaccination, (iii) a hyperlink of a webpage showing clinics in the private sector that provide rotavirus vaccines, (iv) vaccination reminders and (v) contacts of specific community health centres and a token to receive rotavirus vaccines free of charge.

## **7. Safety**

Not applicable as this research does not involve any safety issue. Side effects of rotavirus vaccination are rare, usually mild, and may include fussiness, diarrhoea and vomiting. Some studies have shown a small

increased risk of intussusception within a week after vaccination but the World Health Organization and other health authorities advise that the benefits of rotavirus vaccination far outweigh this risk.

## **8. Statistics**

### **Exposures**

Type of intervention: standard information about rotavirus infection (control group and two intervention groups) plus (i) key information about rotavirus infection and vaccination, (ii) a hyperlink of a webpage showing clinics in the private sector that provide rotavirus vaccines, (iii) vaccination reminders and (iv) contacts of specific community health centres and a token to receive rotavirus vaccines free of charge (intervention group 2 only).

### **Outcome measures**

#### Primary Outcome measure

Uptake rate of rotavirus vaccine in children at 8 months.

#### Secondary Outcome measure

1. Knowledge, attitudes and practices of mothers in relation to rotavirus vaccine before and after receiving control or intervention information.
2. Uptake rate of rotavirus vaccine in children at 8 months by family socioeconomic status.

### **Statistical analysis**

To ensure data quality, the data will be double-entered and validated using EpiData. Intention-to-treat analysis will be used with missing status of rotavirus vaccination taken as no vaccination. An initial univariate analysis will be performed on all variables to derive means, standard deviations and ranges. These initial results will be examined for possible errors and corrected as necessary. To assess the usefulness of the interventions, chi-squared tests will be used to compare rotavirus vaccine uptakes between control and intervention groups. To determine whether removal of financial barriers can increase uptake of rotavirus vaccine in children (study objective 1), we will compare intervention group 2 with the intervention group 1. To determine whether provision of key information on rotavirus infection and vaccination can increase uptake of rotavirus vaccine in children (study objective 2), we will compare intervention group 1 with the control group. We will use multiple regression models to assess the association between the rotavirus vaccination uptake rate and mothers' knowledge and attitudes before and after delivering intervention materials. The models will then be compared to assess the factors influenced by the interventions. To determine the change in knowledge and attitudes after receiving intervention information, permutation tests (16) will be performed on the paired data. All statistical analysis will be performed using statistical software R version 3. 5.2 and a two-tailed p-value <0.05 will be taken as statistically significant.

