### **3. Hypotheses and objectives**

#### **Hypotheses:**

1. The uptake of rotavirus vaccine in Hong Kong is associated with socioeconomic status and removal of financial barriers will increase uptake of the vaccine in all socio-economic groups but proportionately more in the low-income groups.
2. The uptake of rotavirus vaccine in Hong Kong is associated with parents' knowledge and attitudes in relation to rotavirus vaccine and infection and providing key information on rotavirus infection and vaccination will increase uptake of the vaccine.

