## **Data collection**

The study data will be collected at two time-points: (i) a face-to-face interview followed by a self-administered questionnaire at enrolment in postnatal wards; and (ii) an online self-administered questionnaire at children's age of approximately 8 months. In the first questionnaire, we will collect information on the key demographic information and mother's knowledge, attitudes and practices in relation to rotavirus vaccine. In the online questionnaire, we will collect the child's rotavirus vaccination history at 8 months old and an electronic copy of the child's vaccination record card. In addition all participants will be asked about the knowledge, attitudes and practices in relation to rotavirus vaccine. Participants will be followed-up by phone if the final questionnaire is not completed.

Knowledge, attitudes and practices of mothers will be assessed by questionnaires based on Health Belief Model (HBM). The HBM is a simple, widely used framework to explain human health decision-making and behaviour (10;11). It was developed in the 1950s and improved in 1980s (12-14). It contains six concepts to predict how humans make decisions. These include perceived susceptibility and severity of illnesses, perceived benefits and barriers of interventions, cues to action and self-efficacy. The questionnaires are based on previous intervention study to increase influenza vaccine uptake (15). The modified questionnaire will be pilot-tested in approximately 30 mothers at the postnatal wards of the two study hospitals so as to ensure the internal consistency of questionnaire items within constructs is acceptable. Questionnaires will then be refined if necessary.

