## **5. Selection of subjects**

The provision of publicly available information from the CHP about rotavirus infection to all participants may increase their knowledge of the vaccine in subjects who do not know the vaccine before joining the study. To ensure we will have enough sample to examine the study objectives, we assume the baseline rotavirus vaccine uptake would be 40%. We estimate the intervention 2 will increase the subjects' rotavirus vaccine uptake from 40% to at least 55%. Anticipating 20% drop-out, based on a required power of 80% and a significance level of 0.05, by using G\*Power version 3.1.9.2, the sample size required in each group is 262-263, and 788 in total. 459 and 329 subjects will be recruited in the Prince of Wales Hospital and United Christian Hospital respectively.

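### Unadjusted chi-squared tests are the only arm comparison of uptake: valid, but they forgo a modest precision gain and cannot test Hypothesis 1's larger effect in low-income families

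*Protocol*

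**What the plan says.** **Arm comparison.** In Protocol section 8, Statistical analysis, "chi-squared tests will be used to compare rotavirus vaccine uptakes between control and intervention groups". For the financial-barrier objective, "we will compare intervention group 2 with the intervention group 1"; for the information objective, group 1 is compared with control. No covariate is named. Missing vaccination status counts as not vaccinated.

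**Other model of uptake.** The same section says "We will use multiple regression models to assess the association between the rotavirus vaccination uptake rate and mothers' knowledge and attitudes", before and after the materials are delivered. No arm, hospital or socioeconomic term is named there.

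**Hypothesis 1 (section 3).** Removing financial barriers "will increase uptake of the vaccine in all socio-economic groups but proportionately more in the low-income groups".

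**Secondary outcome 2 (section 8).** "Uptake rate of rotavirus vaccine in children at 8 months by family socioeconomic status". No analysis is attached to it.

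**Baseline data and hospitals.** At enrolment, "we will collect information on the key demographic information" together with mothers' knowledge, attitudes and practices (section 4, Data collection). Section 5 fixes hospital numbers: "459 and 329 subjects will be recruited in the Prince of Wales Hospital and United Christian Hospital respectively". Section 4, Methods, describes random blocks of 6 to 12 and states no stratification by hospital.

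**The concern.** Hypothesis 1 has two parts: uptake rises in every socioeconomic group, and it rises proportionately more where income is low. The second part is a statement about effect modification. An overall two-arm chi-squared test carries no information on it, and the regression on knowledge and attitudes is not described as addressing it. Section 2 gives low uptake in lower socioeconomic groups as a particular reason for the trial, so this part should not be left without a pre-stated analysis. Nor does the protocol fix a scale for the word proportionately, and the answer can change with the scale.

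A lesser matter is efficiency. Hospital and the baseline scores will be on file for every participant, and using them in the arm comparison would sharpen it at almost no cost.

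**Working it through.** **1. The plan's own figure.** Section 5 gives 40% to 55%, 80% power, significance level 0.05, 20% drop-out and 262-263 per group. The pooled-variance formula is n = [z_a √(2p̄q̄) + z_b √(p1q1 + p2q2)]² / (p2 − p1)², with 2p̄q̄ = 0.49875 and p1q1 + p2q2 = 0.4875.
- Two-sided 0.05: n = 173, and 173/0.8 gives 217. The stated figure is not reproduced.
- Two-sided 0.025: n = 210, 210/0.8 = 262.5, and 3 × 262.5 = 787.5, so 788. This matches.

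That mismatch is a separate matter. Here I use only the implied sizes: 210 evaluable or 262-263 randomised per group.

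Power for 40% against 55% at 210 per group, alpha 0.05: (0.15 − 1.96 × √(0.49875/210)) / √(0.4875/210) = 1.13, so 87%. If 20% in each arm are missing and counted as unvaccinated, 32% against 44% at 262 per group has about 81%.

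**2. Value of adjustment.** Simulation of 1,500 trials per scenario, 210 per arm, 40% against 55%, with a hospital effect and one continuous baseline predictor. All predictor strengths are assumed.

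| Baseline predictor, odds ratio per SD | Chi-squared power | Adjusted logistic power | Gain (points) |
|---|---|---|---|
| about 1.2 | 85.5% | 87.1% | 1.6 |
| about 1.65 | 86.0% | 88.8% | 2.8 |
| about 2.5 | 87.6% | 92.6% | 5.0 |
| about 3.3, larger hospital effect | 88.3% | 94.0% | 5.7 |

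Type I error was 4.3% to 5.7% across both tests, so adjustment corrects no error-rate problem.

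**3. Hospital alone.** With shares 459/788 = 0.5825 and 0.4175, the SD of the between-arm difference in hospital share is √(2 × 0.5825 × 0.4175 / 263) = 0.043. With an assumed 10-point uptake gap between hospitals, one SD of imbalance moves the estimate by 0.43 points. The standard error is √(0.4875/210) = 4.8 points. The effect is small.

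**4. Power for the Hypothesis 1 interaction.** Assume a median split, so 105 evaluable per cell (210/2) or about 131 if all randomised are analysed. Assume low-income uptake goes from 30% to 50% and high-income from 50% to 55%, a 15-point difference in effects.
- Risk difference: SE = √((0.21 + 0.25 + 0.25 + 0.2475)/105) = 0.095; 0.15/0.0955 = 1.57; power 35%. With 131 per cell, 42%.
- Risk ratio: ln(1.667/1.10) = 0.416; SE = √((2.333 + 1 + 1 + 0.818)/105) = 0.221; power 47%. With 131 per cell, 55%.
- The 131-per-cell figures take uptake as undiluted. If 20% are missing and counted as unvaccinated, all four rates are multiplied by 0.8 and the difference in effects falls to 12 points. Power is then about 30% (risk difference) and 41% (risk ratio).

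Other assumed patterns on the risk-difference scale with 105 per cell give 18% power for a 10-point difference in effects, 39% for 16 and 55% for 20. Reaching 80% would need about 746, 295 and 188 per cell.

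**5. Scale.** Take 30% to 45% in low-income and 50% to 65% in high-income families. The risk differences are equal (15 points each). The risk ratios are 1.5 and 1.3. The odds ratios are 1.91 and 1.86. Hypothesis 1 would look supported on the risk ratio, nearly null on the odds ratio and null on the difference.

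**The case against.** **Chi-squared is a valid test here.** This stands. Randomisation justifies it, and no stratification is stated that would oblige adjustment. The covariate part is an improvement, not the correction of an error.

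**Covariates and interaction models often sit in an analysis plan, which is not shown.** This stands for the covariate list. It is weaker for Hypothesis 1: section 8 ties named tests to named objectives and lists a socioeconomic outcome, yet none of those tests can address the claim. It is also fair that neither aim in section 3 mentions income, which limits the severity.

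**Stronger readings that the documents do not support.**
- *A reader might infer that the baseline predictors are strong.* Section 2 gives a ratio of 1.5 for the highest income quartile. Its coefficients of 0.16 are for perceived benefits and self-efficacy, not uptake. Income is not named among the items collected; some socioeconomic measure is only implied by the secondary outcome.
- *A reader might infer that the contrasts are already under-powered.* A 15-point contrast has 87% power at 210 per group. The documents do not say how large each of the two tested steps will be, so this cannot be shown here.
- *A reader might infer that the plan will compare p-values across income strata.* It says nothing of the kind. The risk is only that the gap gets filled that way. With equal 15-point gains in both strata (30% to 45%, 50% to 65%) and 105 per cell, power is about 61% and 60%, so exactly one stratum is significant with probability 0.61 × 0.40 + 0.60 × 0.39, about 48%.
- *A reader might infer that hospital must be a stratification factor.* Step 3 of the working shows little at stake, and differing access to the free centres by hospital is conjecture.

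**Conclusion.** The point holds in two parts of unequal weight. First, no stated test can assess whether the effect is proportionately larger in low-income families, although Hypothesis 1 asserts it and a secondary outcome points to it. This follows from the text and needs no assumption. Second, the unadjusted comparison gives up about 2 to 6 points of power. That range rests on assumed predictor strengths, and its lower end fits weak predictors.

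A pre-stated interaction would still be imprecise. Power is roughly 18% to 55% on the risk-difference scale for differences in effects of 10 to 20 points, with a median split and 105 per cell, all assumed. It can yield an estimate with an interval, not a confirmatory answer. This is a worthwhile improvement to section 8 and does not threaten the validity of the primary tests.

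**What to change.** In section 8:

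1. Make the arm comparison a logistic model of uptake on arm, hospital, baseline knowledge and attitude scores, and the socioeconomic measure collected. Name the covariates before unblinding. Use the enrolment scores only, since the 8-month scores may be changed by the intervention. Report group 2 against group 1 and group 1 against control as standardised risk differences with 95% CIs. Keep chi-squared as supportive.
2. For Hypothesis 1, fit one interaction of arm by socioeconomic status for group 2 against group 1. Name the risk ratio as its scale, to match proportionately, and give the risk-difference version too. State the socioeconomic measure and how it is coded. Report estimates with CIs and label them exploratory.

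The cost is revised wording, the pre-naming of covariates and slightly more analysis work; no new data or participants are needed beyond the socioeconomic measure that the secondary outcome already implies. Separate allocation lists per hospital are optional and would also change the randomisation text in section 4, Methods.

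### Knowledge and attitudes (secondary outcome 1): both stated analyses compare before with after, and neither compares randomised arms, yet one is used to identify what the interventions influenced

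*Protocol*

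**What the plan says.** The protocol's first secondary outcome is "Knowledge, attitudes and practices of mothers in relation to rotavirus vaccine before and after receiving control or intervention information" (Section 8, Secondary Outcome measure).

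The Statistical analysis part of Section 8 treats uptake and knowledge differently.

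- **Uptake.** "chi-squared tests will be used to compare rotavirus vaccine uptakes between control and intervention groups". Two contrasts are named: group 2 against group 1 for the financial barrier, and group 1 against control for the information.
- **Knowledge and attitudes, regression.** Uptake is related to mothers' "knowledge and attitudes before and after delivering intervention materials". Then: "The models will then be compared to assess the factors influenced by the interventions".
- **Knowledge and attitudes, change.** "To determine the change in knowledge and attitudes after receiving intervention information", "permutation tests (16) will be performed on the paired data". Results with a two-tailed p below 0.05 count as significant throughout.

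No sentence compares knowledge, attitudes or their change between randomised arms.

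Three other places bear on the point. Section 4 (Methods) has the enrolment questionnaire completed first, then allocation, then the standard information handed to families in every group. Section 4 (Data collection) asks all participants about knowledge and attitudes again at about 8 months, in the same online questionnaire that records vaccination history. Section 5 says that giving the public leaflet to everyone "may increase their knowledge of the vaccine in subjects who do not know the vaccine before joining the study".

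**The concern.** A paired test asks whether mothers changed between the postnatal ward and 8 months. It does not ask whether they changed more in one arm than in another. At least three things can move scores in every arm, control included: the leaflet given after the baseline questionnaire, answering the same kind of questionnaire twice, and 8 months of caring for an infant. The paired test absorbs all of them together with any intervention effect.

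The model comparison has the same gap and a second one. If a knowledge item is related to uptake more strongly at 8 months than at enrolment, an association has changed. That does not show that an intervention moved the item. The 8-month scores are also collected after the vaccination decision, since the protocol gives 8 months as the upper age for the vaccine. Having vaccinated, or not, may shape the answers.

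At stake is the trial's evidence on how the information package works, which is the mechanism behind hypothesis 2. Followed as written, the analysis could credit the interventions with changes that are the same in all three arms.

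**Working it through.** **Plan's own figure.** There is none. The protocol gives no expected size of change and no power for this outcome, so the size below is an illustration on assumed inputs.

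**Inputs**
- Pairs per arm: 788 / 3 = 262.67 enrolled; with the 20% drop-out of Section 5, 262.67 × 0.8 = 210.
- Two-sided alpha 0.05 (Section 8).
- Assumed: pre-post correlation ρ = 0.5, and a change δ (in SD of the score) that is equal in all three arms, so the intervention effect is zero.

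**Within-arm paired test.** The change score has SD √(2(1−ρ)) = 1 at ρ = 0.5, so z = δ × √210 / √(2(1−ρ)) = 14.49 δ. The chance of significance is about Φ(z − 1.96).

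| δ | z | Significant within an arm (formula) | Simulation |
|---|---|---|---|
| 0 | 0 | 5% (both tails) | 5% |
| 0.1 | 1.45 | Φ(−0.51) = 30% | 31% |
| 0.2 | 2.90 | Φ(0.94) = 83% | 83% |
| 0.3 | 4.35 | Φ(2.39) = 99% | 99% |

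The simulation used 4,000 runs, with a one-sample t-test on change scores standing in for the paired test. A sign-flip permutation test, closer to what the protocol names, gave 4.5%, 28.5% and 82% at δ = 0, 0.1 and 0.2 (400 runs each).

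**Sensitivity to the correlation, δ = 0.2.** At ρ = 0.3, z = 2.90 / √1.4 = 2.45, giving Φ(0.49) = 69%. At ρ = 0.7, z = 2.90 / √0.6 = 3.74, giving Φ(1.78) = 96%.

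**Between-arm comparison.** With an equal change in both arms the expected difference is zero. In the same simulation the test of the difference in mean change was significant in 4.6% to 5.5% of trials, whatever the size of the shared change.

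**If the paired tests are run arm by arm and read side by side.** With p the within-arm chance above, two arms disagree on significance with probability 2p(1−p):
- δ = 0.1: 2 × 0.305 × 0.695 = 42% (simulation 43%)
- δ = 0.15: z = 2.17, p = Φ(0.21) = 0.585, so 2 × 0.585 × 0.415 = 49%
- δ = 0.2: 2 × 0.826 × 0.174 = 29% (simulation 28%)

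A result that is significant in group 1 but not in control is therefore common when the arms do not differ at all. Testing by arm does not close the gap.

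**The case against.** The case on the other side has force on several points.

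- **The paired test answers its own question.** The sentence that introduces it promises only to determine change. In the scenarios above mothers did change, so a significant result is correct as a statement about change. This stands. The 83% and 99% are not error rates of the paired test; they say how often shared change would be wrongly attributed by someone who reads the result as an intervention effect. The causal wording is in the model-comparison sentence.
- **The protocol does not exclude an arm comparison.** The outcome covers change "before and after receiving control or intervention information", which suggests reporting in every arm. It is not stated whether the paired tests are pooled or run by arm, an arm term in the regressions is not ruled out, and an analysis plan not at hand could add one. This also stands. A reader might infer that the randomisation is discarded for this outcome. The text supports only that the analyses it names do not compare arms. What remains is that the protocol fixes a method and draws an intervention inference from it; that is more than a detail left open.
- **The regressions are described as assessing association.** True of that sentence, which states no direction. The next sentence goes further and reads the comparison of models as showing what the interventions influenced.
- **Section 5 is cautious.** A reader might take it to predict a rise in control knowledge. It says only that knowledge may increase, in mothers who did not know the vaccine beforehand, and says so in setting the 40% uptake assumption. It makes shared change plausible, no more.

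**Conclusion.** The point holds for secondary outcome 1. As written, the protocol has no stated test of whether the interventions changed knowledge or attitudes, and it draws that inference from a comparison of before and after models that contains no stated arm contrast. The paired tests describe change and cannot attribute it.

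The illustrated size is about 83% significant within-arm results at a shared change of 0.2 SD, against about 5% between arms. It rests on assumed values (correlation 0.5, 210 completers per arm, equal change in all arms); over shared changes of 0.1 to 0.3 SD the within-arm figure runs from about 30% to 99%. The logical gap does not depend on these values.

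A reader might infer that the trial's main conclusions are at risk. They are not. Both aims and the primary outcome concern uptake, which is compared between randomised arms. Allocation, data collection and sample size are untouched. This should be fixed, as a matter of wording for a secondary analysis.

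**What to change.** In Section 8, Statistical analysis:

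1. Test intervention effects on knowledge and attitudes by comparing 8-month scores between arms, adjusted for the enrolment score. Use the contrasts already fixed for uptake: group 1 against control, and group 2 against group 1.
2. If a permutation p-value is wanted, permute arm labels in a way consistent with the randomisation scheme. The protocol describes random blocks and does not state stratification by hospital, so permuting within hospital should not be presumed.
3. Keep the paired permutation tests, run by arm and described as within-arm change.
4. Label the regression of uptake on 8-month scores as descriptive association, and remove the statement that comparing the before and after models shows which factors the interventions influenced.

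The cost is a few sentences. Enrolment and 8-month scores are already planned for all participants, and the planned software suffices.

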## **Methods**

Mothers will be enrolled in the study at the postnatal wards of two public hospitals (Prince of Wales Hospital and United Christian Hospital). After consent has been obtained and questionnaires have been completed, a study Research Assistant (RA) not involved with other follow-ups will randomly allocate all participants to either control or two intervention groups using block randomisation with 1:1:1 ratio (9). Each group will have 262-263 participants. We will use statistical software R version 3.5.2 to randomly generate the intervention allocation in random block sizes of 6 to 12 with block size kept unknown to investigators and the RA carrying out interviews. This precaution maintains concealment. Once the intervention has been allocated, this RA will not be blinded to participants' group assignment, but the other RA conducting telephone interviews, investigators and participants will be blinded to participants' group allocation. Families in all groups will then be given an envelope containing the standard information about rotavirus infection. The intervention group 1 will receive additional information about rotavirus infection and vaccination and a hyperlink of a webpage showing clinics in the private sector that provide rotavirus vaccines by post one to two days after discharge from hospital and a RA will call and explain the information within a month after the package sent. Then a text message reminder at the children's age of 6 to 8 weeks will be provided. The intervention group 2 will receive the same information as the intervention group 1, and additionally be given information on how to contact a specific UCN health centre where they can receive rotavirus vaccine free of charge and in reasonable proximity to their home.

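### Each contrast of the one primary outcome is judged at two-sided 0.05 with no order, gate or split, and the sample size of 788 matches 0.025 rather than the stated 0.05

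*Protocol*

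**What the plan says.** The protocol has one primary outcome (Section 8, Primary Outcome measure) and three arms, allocated "using block randomisation with 1:1:1 ratio" (Section 4, Methods). Group 2 receives everything group 1 receives plus free vaccine, so the arms are nested.

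Section 8, Statistical analysis, gives each aim its own contrast: group 2 against group 1 for removing the financial barrier, and group 1 against control for providing information. A preceding sentence says that "chi-squared tests will be used to compare rotavirus vaccine uptakes between control and intervention groups". One threshold covers all analyses: "a two-tailed p-value <0.05 will be taken as statistically significant". No testing order, gatekeeping step or division of alpha is given.

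Section 5 sizes the trial for a rise from 40% to 55% under intervention 2, "based on a required power of 80% and a significance level of 0.05". After "Anticipating 20% drop-out" it concludes that "the sample size required in each group is 262-263, and 788 in total". It mentions no split of the 0.05.

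**The concern.** Two or three tests of the same outcome, in arms that share participants, each have their own 5% chance of a false positive. The two aim contrasts both use group 1, so an unusually high or low result in that arm by chance affects both. With the full 0.05 allowed for each test and no rule linking them, the 5% does not hold for the set of primary conclusions.

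The sample size adds a problem internal to the protocol. Its total does not follow from the alpha it states, but it does follow from half that alpha. Sections 5 and 8 may therefore have been written with different error rates in mind, and a reader cannot tell which one governs the trial.

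**Working it through.** **1. The plan's own figure.** Inputs from Section 5: p1 = 0.40, p2 = 0.55, power 80%, significance level 0.05, drop-out 20%. Two-sidedness comes from Section 8. With mean proportion 0.475, the evaluable number per arm is

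n = [z(1−α/2)·√(2·0.475·0.525) + 0.8416·√(0.40·0.60 + 0.55·0.45)]² / 0.15²

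- α = 0.05 (z = 1.960): (1.3842 + 0.5876)² / 0.0225 = 172.8, so 173. Then 173/0.8 = 216.25 per arm and 3 × 216.25 = 648.75 in total (651 if each arm is rounded up to 217).
- α = 0.025 (z = 2.241): (1.5829 + 0.5876)² / 0.0225 = 209.4, so 210. Then 210/0.8 = 262.5 per arm and 3 × 262.5 = 787.5, so 788.

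The second line reproduces both the 262-263 per group and the total. Other methods at unsplit 0.05 do not: a continuity correction gives 186 evaluable (233 per arm, 699 in total), Fisher's exact test about 183 (229 per arm), and a one-sided test 136 (170 per arm, 510 in total). A three-arm 2-df test at 0.05 with group 1 midway comes close, at 641 evaluable in total and 641/0.8 = 801, but does not give 788.

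**2. Error rate if neither component works.** All tests are at two-sided 0.05.

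| Set of tests | If independent | Simulated, 3 arms of 263 |
|---|---|---|
| Two aim contrasts | 1 − 0.95² = 9.75% | 9.0% (uptake 40%), 9.1% (32%) |
| All three pairs | 1 − 0.95³ = 14.3% | 12.1% (40%), 12.3% (32%) |
| All three pairs after a 2-df test at 0.05 | n/a | 5.0% |

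A normal approximation with 4,000,000 draws gives 9.1% and 12.2%. The studentized range distribution gives 12.2% for three pairs.

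**3. Error rate if one component works.** With control and group 1 at 40% and group 2 at 55%, only one aim hypothesis is null. It is rejected in 5.0% of simulated trials (5.1% at 32%, 32% and 44%).

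**4. Power cost of the remedies** (1,000,000 simulated trials per row, 263 per arm). The lower uptakes apply Section 8's rule that missing status counts as unvaccinated. They assume 20% missing equally in every arm: 0.8 × 40% = 32% and 0.8 × 55% = 44%.

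| Control, group 1, group 2 | Contrast | Unadjusted | Three-arm gate | Holm on the aim contrasts |
|---|---|---|---|---|
| 40, 40, 55% | 2 vs 1 | 93.3% | 92.0% | 89.2% |
| 32, 32, 44% | 2 vs 1 | 81.5% | 77.5% | 72.8% |
| 40, 47.5, 55% | 2 vs control | 93.3% | 87.7% | not in family |
| 32, 38, 44% | 2 vs control | 81.4% | 70.9% | not in family |

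**The case against.** The strongest reply is that Section 3 states two distinct hypotheses and aims, each with its own contrast. A positive result for free vaccine cannot be claimed for the information aim, and the protocol nowhere defines overall success as any positive contrast. Whether separate, pre-assigned aims need family-wise control is a debated convention. This reply has weight and argues against calling the plan plainly wrong. It is weakened here by the nested arms, the shared group 1, the single outcome and a sample size that matches a halved alpha.

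A reader might infer more than the protocol supports on four points:

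- **That the sample size has already paid for a split alpha.** Section 5 states 0.05 and no split; the split appears only in the arithmetic. It also fails for the planned analysis. With drop-outs counted as unvaccinated (32% against 44%), 256 per arm are needed at 0.05 but 310 at 0.025, against the planned 262-263.
- **That Holm on the two aim contrasts matches the sizing.** Section 5 describes intervention 2 against a 40% baseline, most naturally group 2 against control, and that contrast is outside the Holm family.
- **That three pairwise tests are certain.** The general chi-squared sentence may only name the method, or may announce a pooled or three-arm test. The 12% belongs to one reading.
- **That 9-12% applies whatever the truth.** It holds only if neither component works.

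Multiplicity is often left to an analysis plan, which is not available here. That would excuse silence, but this protocol positively sets 0.05 for every analysis.

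**Conclusion.** The point stands in limited form. Section 8 allows each contrast of the primary outcome the full two-sided 0.05. The family-wise error is then about 9% for the two aim contrasts, and up to about 12% if all three pairs are tested. Both figures assume that neither component has any effect. Where one component works, the remaining aim contrast keeps its 5%.

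Separately, 788 does not follow from the 0.05 stated in Section 5, which gives about 650 by the standard formula. It matches two-sided 0.025 exactly. That an adjustment over two comparisons was intended is a reasonable inference, not something the protocol says. What is firm is that the stated alpha and the stated size disagree and must be reconciled.

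**What to change.** In Section 8, name the primary contrasts and say whether group 2 against control is one of them. Test the three arms together first with a 2-df chi-squared test at 0.05, and go on to the pairwise tests at 0.05 only if it is significant. For three arms this is a closed procedure, so it controls the family-wise error at 5% (to the accuracy of the chi-squared approximation) whichever components work. In Section 5, state the alpha and the contrast actually used for the size.

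The text change is a few sentences and one extra test. By the last table under the working, the gate costs group 2 against group 1 about 1 to 4 points of power when group 1 equals control. It costs group 2 against control about 6 to 10 points when group 1 lies midway.

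Holm on the two aim contrasts is an alternative. It costs about 4 to 9 points on the contrast that carries the effect and leaves out group 2 against control, so it should not be presented as free.
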